## Abstract

**Background:**

Celecoxib is frequently prescribed to treat knee osteoarthritis (KOA), but how celecoxib influences the activity of the central nervous system to alleviate chronic pain remains unclear.

**Methods:**

One hundred eight patients with KOA will be enrolled in this study. Patients will be allocated randomly to three groups: the celecoxib group, the placebo group, and the waiting list group. The patients in the celecoxib group will orally take celecoxib 200 mg once daily and the patients in placebo group with placebo 200 mg every day for 2 weeks. Functional magnetic resonance imaging scan will be performed on all patients at baseline and the end of interventions to detect the cerebral activity changes. The short form of McGill pain questionnaire and the Visual Analog Scale will be used as the primary endpoints to evaluate the improvement of knee pain. The secondary endpoints include the Western Ontario and McMaster osteoarthritis index (WOMAC), the Attention Test Scale, the Pain Assessment of Sphygmomanometer, the Self-rating Anxiety Scale, the Self-rating Depression Scale, and 12-Item Short Form Health Survey (SF-12).

**Discussion:**

The results will investigate the influence of celecoxib treatment on cerebral activity of patients with KOA and the possible relationship between the cerebral activity changes and improvement of clinical variables so as to explore the central mechanism of celecoxib in treating knee pain.

**Trial registration:**

ChiCTR-IOR-17012365. Registered on August 14, 2017.

**Electronic supplementary material:**

The online version of this article (10.1186/s13063-018-3111-8) contains supplementary material, which is available to authorized users.

## Background

Non-steroidal anti-inflammatory drugs (NSAIDs), known as cyclooxygenase (COX) inhibitors, are often prescribed for the management of chronic and acute pain worldwide. NSAIDs exert analgesic effects by inhibiting COX activity in the arachidonic acid cascade and thus inhibit prostaglandin (PG) synthesis [1], which leads to a reduction or reversal of peripheral sensitization. Based on the results of animal studies, NSAIDs could also modulate pain intensity by suppressing prostanoid formation in the spinal cord and brain [2, 3], thus affecting central sensitization. On human beings, the peripheral action of NSAIDs for pain management had been well investigated. For instance, Gallelli et al. found that diclofenac, ibuprofen, and celecoxib can decrease tumor necrosis factor-alpha (TNF-α), interleukin-6 (IL-6), and vascular endothelial growth factor in the synovial fluid of the osteoarthritic joint with a parallel improvement in joint pain and function of patients [4]. However, the central action of NSAIDs is less studied, and the majority of these studies performed on healthy subjects or centered on acute pain condition. For example, neuroimaging studies found that instant NSAIDs could attenuate the activity on pain processing cerebral structures in healthy subjects [5] and top-down modulatory circuits in acute pain condition [6]. How the NSAID drugs acting on the central nervous system (CNS) in patients with chronic pain remains unclear and is worthy of further investigation.

Celecoxib, as the first COX-2 selective inhibitor, was introduced into clinical practice nearly 20 years ago [7–9] and widely used for many pain conditions for fewer side effects. It was reported that, compared with other NSAIDs such as ibuprofen and diclofenac at standard dosages, celecoxib was associated with a lower incidence of symptomatic ulcers and ulcer complications and other clinically important toxic effects [10].

As a high prevalence chronic knee pain [11], the prevalence of radiographic knee osteoarthritis was 19% and 28% among adults over 45 years old in Framingham study and Johnston County Osteoarthritis Project [12]. With the aging of the population, most patients with KOA visit a doctor for their pain treatment [13, 14]. KOA has become the leading cause of disability in the world and brings an increasingly high social and economic burden [15, 16]. Meta-analysis has already indicated that celecoxib treatment (200 mg orally once daily) led to significant improvement in the pain and knee function of patients with osteoarthritis [17]. Although celecoxib treatment is effective for pain management in KOA, little is known about how celecoxib treatment modulates the activity of CNS to alleviate pain in patients with KOA.

With the application of neuroimaging techniques in pain research, investigators not only mapped the brain regions which are involved in the central pathogenesis of chronic pain but also can explore the cerebral responses elicited by analgesics so as to illuminate the central mechanism. With resting-state functional magnetic resonance imaging (rs-fMRI), investigators found that the patients with chronic pain demonstrated the alternations in functional connectivity (FC) of medial prefrontal-default mode network and the regional homogeneity (ReHo) value changes of anterior cingulate cortex [18–21].

These results greatly enhance the understanding of the central mechanism of chronic pain and provide a new approach to the research and development of drugs. For instance, Xiaoyan Chen et al. had shown that acupuncture can regulate the descending pain modulatory system of patients with KOA by enhancing the FC between the right frontoparietal network and medial prefrontal cortex [22].

So this trial aims to (1) investigate the influence of celecoxib treatment on the brain activities of patients with KOA compared with that of placebo treatment and waiting list by fMRI and (2) analyze the possible correlations between the changes of cerebral activity and the improvement of clinical variables in each group so as to explore how the celecoxib manages pain by modulating brain function to treat KOA.

## Design and methods

### Study design

This is a clinical neuroimaging study aiming to investigate the central mechanism of how celecoxib alleviates knee pain for treating KOA. A total of 108 patients with KOA will be randomly allocated to three different groups. Each group includes 36 patients with KOA. The three groups are group A (celecoxib administrated orally once a day), group B (placebo administrated orally once a day), and group C (waiting list). The treatment period will last for 2 weeks. Outcome measurements and MRI scan will be assessed at baseline and at the end of treatment. The changes of clinical variables and cerebral activity of each group will be analyzed after data collection (Fig. 1).

**Fig. 1 Fig1:**
[figure not shown]
Flowchart of the trial. Abbreviation: *MRI* magnetic resonance imaging

### Participants

Knee pain patients whose KOA is diagnosed according to American College of Rheumatology (ACR) criteria (1991 revised version) [23] will be recruited from outpatient or inpatient departments of the First Affiliated Hospital of Chengdu University of Traditional Chinese Medicine (TCM) and the Third Affiliated Hospital of Chengdu University of TCM. Potential patients will also be recruited through posters, internet, and leaflets.

### Inclusion criteria

Inclusion criteria require that the patients (1) match the diagnosis criteria for KOA set by ACR in 1991 [23], (2) are between 40 and 60 years of age and are right-handed, (3) have not taken any pain killer medicine within 1 month, (4) have at least 3 months of knee pain duration, (5) have an average score on the knee pain Visual Analog Scale (VAS) of at least 3 cm (range of 0 to 10 cm) in the past 2 weeks, (6) have knee joint radiological degree of 0–II in accordance with the Kellgren–Lawrence scale [24], and (7) have signed a written informed consent form.

### Exclusion criteria

Patients will be excluded if they (1) are alcohol or drug abusers or abuse other medications that may influence brain imaging outcomes; (2) are pregnant or lactating; (3) have psychiatric, neurologic, gastrointestinal, cardiovascular, infectious, immunologic, respiratory, or renal illnesses; (4) have any other chronic pain conditions or a history of head trauma with loss of consciousness; (5) had diagnosed rheumatoid arthritis or other leg-related pain disorders; (6) have MRI contraindications such as claustrophobia, cardiac pacemaker, defibrillator, heart stenting, or intrauterine device; (7) have active peptic ulcer or a history of peptic ulcer; or (8) are allergic to celecoxib.

### Sample size

The sample size calculation of neuroimaging study is different from that of classic randomized controlled trials. The neuroimaging study focuses on investigating mechanism but not evaluating efficacy. General speaking, in MRI studies, 12 to 15 patients per group provide a statistical result [24, 25]. Our previous literature study shows that at least 20 patients per group can achieve stable results for brain functional network analysis [26]. In this study, we require 30 patients per group in this trial. However, considering a 20% dropout rate and possible excessive head motion during scanning, we will include 36 participants with KOA in each group. Finally, we plan to enroll 108 participants and each group will undergo MRI scans twice to investigate the different central responses among celecoxib, placebo, and waiting list treatment in knee pain KOA patients.

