### Randomization

Eligible patients will be randomly assigned in a ratio of 1:1:1 to the celecoxib group, placebo group, and waiting list group with 36 patients in each group. Random number lists will be created in accordance with PROC PLAN of SAS 9.2 (SAS Institute Inc., Cary, NC, USA). The randomization allocation will use sequentially numbered, opaque, and sealed envelopes by an independent assistant. The celecoxib group and the placebo group will be concealed from the researchers until completion of the statistical analysis.

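### 36 per group does not yield the required 30 at the stated 20% loss (36 × 0.8 = 28.8); a minor error that restating the figure corrects

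*Protocol article*

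**What the plan says.** The Sample size section of the protocol article gives three linked figures.

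- The requirement: "In this study, we require 30 patients per group in this trial".
- The allowance and the enrolment it leads to: "considering a 20% dropout rate and possible excessive head motion during scanning, we will include 36 participants with KOA in each group".
- The total: "Finally, we plan to enroll 108 participants and each group will undergo MRI scans twice".

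The Randomization section uses the same group size: patients are "randomly assigned in a ratio of 1:1:1 to the celecoxib group, placebo group, and waiting list group with 36 patients in each group". Study design also repeats 36 per group, and the Abstract repeats 108 in total. So 36 is the operative design figure, and no other section corrects it.

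The 30 is not derived from an effect size, standard deviation, significance level or power. It is chosen after general remarks on imaging studies, including that "at least 20 patients per group can achieve stable results for brain functional network analysis". No rate is given for scans lost to head motion.

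**The concern.** The enrolment figure is there to deliver the required number after losses. If the plan's own loss rate is applied to its own enrolment figure and the result is below the requirement, the Sample size section claims something the design does not provide.

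The 30 is the only evaluable-size target a reader is given. Anyone who later compares the analysed numbers with the plan will use it, and at the planned loss rate the trial would be expected to miss it.

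Head motion adds an ambiguity. Each patient is scanned twice, and the imaging analysis described under Data analysis uses the change from before to after treatment, so one unusable scan removes the patient from that analysis. The text does not say whether such losses are part of the 20%.

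**Working it through.** **Inputs, all from the Sample size section:** required number per group, 30; loss rate, 20%; enrolled per group, 36; total, 108.

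**1. Reproducing the plan's figure.** Adding 20% to the requirement gives 30 × (1 + 0.20) = 36, and 3 × 36 = 108. Both match the protocol exactly, so this is probably how the figure was obtained.

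**2. Checking it against the requirement.** Expected remaining = enrolled × (1 − loss) = 36 × 0.80 = 28.8 per group, against 30. Over three groups: 108 × 0.80 = 86.4, against 90. The shortfall is 30 − 28.8 = 1.2 patients per group.

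**3. The allowance that would meet it.** Enrolled = required/(1 − loss) = 30/0.80 = 37.5, rounded up to 38 per group, or 3 × 38 = 114 in total. That is 2 more per group and 6 more overall (6/108 = 5.6%).

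**4. The loss that 36 can absorb.** (36 − 30)/36 = 6/36 = 16.7%.

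**5. How likely the target is at 20% loss.** Assume that each patient is lost independently with probability 0.20. Then the number remaining in a group is binomial with n = 36 and p = 0.80, and P(at least 30 remain) = 0.40. If losses are also equal and independent across groups, the chance that all three keep at least 30 is 0.4007³ = 0.064. These probabilities rest on the independence assumption; steps 2 to 4 do not.

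**6. Head motion.** The protocol gives no rate, so this step is illustrative only. If the 20% already includes head-motion exclusions, the expected number stays at 28.8. If it does not, and an assumed 5% to 10% of completers are lost as well, the number for the imaging analyses is 28.8 × 0.95 = 27.4 down to 28.8 × 0.90 = 25.9. The clinical comparisons stay at 28.8, because they do not need a usable scan.

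**The case against.** The strongest reply is that nothing much depends on the difference. The requirement of 30 is a round choice with no power calculation behind it, no decision rule refers to it, and the gap is 1.2 patients per group. The expected 28.8 is well above the 20 per group that the protocol cites for stable network results; so is 25.9, the low end of the illustrative head-motion range. This stands, and it is why the point is minor. It does not remove the inconsistency: the protocol chose 30, not 20, as this trial's requirement, and its own numbers do not reach it.

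A second reply is that the 20% may be a single allowance for dropout and head motion together. The sentence can be read that way. Even so, 28.8 is below 30.

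A third is that a journal article leaves detail to the full protocol. Here the article states the requirement, the loss rate and the enrolment itself, and they conflict. This is a stated error, not an omission.

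A reader might infer three stronger things that the document does not support:

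- **That head motion is certainly an extra loss with no allowance.** That is only one reading of the sentence, and any figure for it comes from outside the protocol.
- **That every analysis will run on fewer than 30.** The 20% is a planning allowance, not a known loss. Even at 20%, a single group keeps at least 30 with probability about 0.40 under independent losses, and head-motion exclusions do not touch the clinical comparisons.
- **That the trial is underpowered as a result.** No power was claimed for 30, so no loss of power can be derived.

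**Conclusion.** The point holds as a minor arithmetic error. On the protocol's own figures, 36 per group is expected to leave 28.8 patients at 20% loss, 1.2 short of the required 30, and it meets the requirement only if total loss is at most 16.7%. This rests on the usual reading of a 20% dropout rate as 20% of those enrolled. It needs no assumption about head motion.

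Whether the imaging analyses fall further short depends on whether the 20% covers head-motion exclusions, which the text leaves open, and on a rate it does not give. The design is not undermined: the expected number remains above the protocol's own benchmark of 20 per group.

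**What to change.** Restate the Sample size section without enrolling more patients. Suggested wording:

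> With 36 per group we expect about 29 evaluable patients per group at 20% total loss. The target of 30 is met only if total loss, including head motion, is at most 16.7%.

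Add one sentence saying whether the 20% includes patients excluded for head motion. If it does not, say that the number available for the imaging analyses will be lower than the number for the clinical comparisons.

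The cost is wording only, and the stated evaluable number becomes slightly less favourable. Enrolling 38 per group (114 in total) would also reconcile the figures if the 20% is the total loss, but a shortfall of this size does not call for it.

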### Informed consent

This study protocol has been approved by the supervision of the Sichuan Regional Ethics Review Committee on TCM (ethical approval number 2016KL-017) and been registered at Chinese Clinical Trial Registry (registration number ChiCTR-IOR-17012365). The authors retain full control of the article’s content. All patients will be informed of the random allocation of celecoxib, placebo, or waiting list treatment and the possible risks. They will voluntarily sign an informed consent form before enrollment. The patients will be free to withdraw from the study at any time without a specific reason and without any penalty or loss of benefits. However, we will attempt to understand the reason for withdrawal and encourage the participant to remain in the study if possible.

### Patient safety

This study will be performed in accordance with the guidance and principles of the Declaration of Helsinki. Adverse events caused by celecoxib, such as nausea, vomiting, or other severe events, will be processed immediately and recorded in detail in the case report forms. Each patient will get paid for study participation. Figure 2 provides a complete overview of the time schedule of the enrollment, interventions, and assessments.

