### Blinding

As waiting list group without any medical intervention, while the other two groups will be given celecoxib or placebo 200mg daily, it is impossible to blind the patients, clinicians and investigators totally. Patients and researchers of the celecoxib group and the placebo group will be unaware of the assignments until completion of the statistical analysis. Only an independent researcher in the pharmacy department knows the allocation of the celecoxib and placebo groups. The evaluators and statisticians will be blinded to the group allocation during outcome evaluation and data analysis to reduce the risk of bias.

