### Interventions

Patients in the celecoxib group will orally take a celecoxib capsule (approval number J20030098, manufactured by Pfizer Pharmaceutical Co. Ltd., Beijing, China) at a daily dosage of 200 mg for 2 weeks. Patients in the placebo group will receive a placebo capsule (manufactured by pharmacy department of Affiliated Hospital of Chengdu University of TCM) with oral administration at the same dosage as celecoxib capsule once a day for 2 weeks. The placebo capsule is identical in appearance, smell, and texture to the celecoxib capsule. Patients in the waiting list group will be observed for 2 weeks without any medical or other interventions. After 2 weeks’ observation, patients in the waiting list group and placebo group could choose either 2 weeks’ celecoxib treatment or acupuncture treatments free of charge.

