### Data management

The case report form includes observation time points, scanning time points, outcome measures, adverse events, and safety evaluations. The researchers will be required to follow the requirements of the case report form and fill in the relevant information in a timely and accurate manner. Data collection will be performed by study physician, and the quality of the data will be supervised by two independent experienced clinical researchers.

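### The adverse-event recording commitment is worded around events attributed to celecoxib, which blinded staff cannot determine and which is narrower than the case report form

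*Protocol article*

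**What the plan says.** The Patient safety section of the protocol article contains the only text on how adverse events are handled: "Adverse events caused by celecoxib, such as nausea, vomiting, or other severe events, will be processed immediately and recorded in detail". It names the case report forms as the place of recording.

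Three other sections bear on it:

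- **Blinding.** For the two capsule arms, "Patients and researchers of the celecoxib group and the placebo group will be unaware of the assignments until completion of the statistical analysis". Further, "Only an independent researcher in the pharmacy department knows the allocation of the celecoxib and placebo groups". Because the waiting list receives nothing, the section concedes that "it is impossible to blind the patients, clinicians and investigators totally".
- **Interventions.** "Patients in the waiting list group will be observed for 2 weeks without any medical or other interventions". Afterwards, placebo and waiting-list patients may choose celecoxib or acupuncture.
- **Data management.** "The case report form includes observation time points, scanning time points, outcome measures, adverse events, and safety evaluations". On who fills it in: "Data collection will be performed by study physician".

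The Concomitant medications section permits ibuprofen as rescue for severe knee pain and does not restrict it to one arm.

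**The concern.** Whether an event happened and whether the study drug caused it are separate questions, and a blinded trial should record the first before asking the second. Here the stated commitment joins them: the events described as recorded are those that celecoxib caused. The person collecting the data would need to know that the patient took celecoxib, which the design withholds, and would then have to attribute the event to it.

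What is at stake is the completeness and evenness of safety data. An event that a physician thinks is unrelated, or that follows rescue ibuprofen, has no clear route onto the form under this wording. If the causal guess is easier to rule out in one arm than in another, recorded frequencies will differ by arm for reasons unrelated to the treatments. Events not written down during the trial may not be recoverable later.

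**Working it through.** The plan gives no adverse-event figure to reproduce, so the check is a comparison of sections, with a count of patients by arm.

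**Inputs**
- Allocation (Randomization): 1:1:1, 36 per arm, 3 × 36 = 108.
- Recording criterion (Patient safety): events attributed to celecoxib.
- Form content (Data management): adverse events and safety evaluations, with no limit by cause or arm.
- Who knows celecoxib from placebo (Blinding): one pharmacy researcher.
- Who collects data (Data management): the study physician.
- Other drug exposure (Concomitant medications): ibuprofen, possible in any arm.

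**Step 1: scope against the form.** Patient safety restricts by cause; Data management does not. The first says which events go in, and the second says that a place for them exists. The two differ in scope, and nothing in the article says which governs.

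**Step 2: can the criterion be applied in the capsule arms?** These hold 36 + 36 = 72 patients. The study physician cannot tell celecoxib from placebo, so cannot establish celecoxib as the cause in any of the 72. The most the physician can do is suspect it, on the same information in both arms.

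**Step 3: can it be applied in the waiting list?** These 36 patients (36/108, one third) receive no study drug during the 2 weeks. No event in that period can satisfy the criterion, and staff may know this, since the article says blinding cannot be total because of this arm.

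**Step 4: rescue medication.** An event due to ibuprofen is not due to celecoxib, so the criterion does not reach it in any arm.

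**Step 5: direction of the effect.** Let r be a true event rate common to all arms, p the share of events recorded in capsule patients, and q the share recorded in waiting-list patients. Expected patients with a recorded event are 36 × r × p in each capsule arm and 36 × r × q in the waiting list, so the artificial difference is 36 × r × (p − q). Blinded suspicion gives the celecoxib and placebo arms the same p, so no artificial difference between those two follows from the wording. Staff who know a patient is off drug would probably record less, giving q below p. With the criterion applied to the letter, q = 0. The article supplies none of r, p or q, so the direction can be argued but the size cannot be computed.

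**The case against.** The strongest reply is that the sentence is loosely worded and not exclusive. It does not say that other events go unrecorded, and it can be read as a promise of prompt handling and detailed recording of drug reactions. The form lists adverse events without restriction, and no separate form for one arm is described. The article also names no safety endpoint and describes no comparison of adverse events between arms, and it presents the study as mechanistic. Finally, a journal article commonly leaves definitions, solicitation and causality procedures to the full protocol.

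Much of this stands, and it rules out three stronger readings that a reader might infer:

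- *That 72 of 108 patients (36 placebo + 36 waiting list) will have no adverse-event record.* Excluding the placebo patients would require recorders who know the capsule allocation, and the unrestricted form content points the other way.
- *That a false drug effect against placebo would appear.* Suppose 10% of each arm had nausea unrelated to drug: 0.10 × 36 = 3.6, so about 3 to 4 celecoxib patients recorded against none elsewhere. That again needs unblinded recorders, and the literal wording would not record unrelated nausea in the celecoxib arm either.
- *That the blind will be eroded by guessing from symptoms.* This is possible, but nothing in the article demonstrates it.

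What the reply does not remove is the stated criterion itself. The complaint is not that detail is missing. The one criterion given is tied to a cause that the blinding conceals, and it disagrees in scope with the description of the form.

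**Conclusion.** The point holds as a badly worded rule that needs reconciling. The recording commitment is conditioned on causation by celecoxib; it is narrower than the form, cannot be applied by blinded staff to the 72 capsule patients, and does not reach events in the 36 waiting-list patients during their 2 weeks or events due to rescue ibuprofen.

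Followed literally, capture depends on a guess and would probably be lower in the waiting list. This conclusion assumes that staff would follow the specific sentence over the general description of the form, and that they know who is on the waiting list. The article confirms neither assumption outright. No numerical bias can be given, and because no between-arm safety analysis is described, the consequence is incomplete safety capture and uneven data for any later tabulation. No planned test is shown to be invalid. The change is worth making because it is cheap and unrecorded events may be lost for good.

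**What to change.** Reconcile the Patient safety, Blinding and Data management sections with one statement: all adverse events in all three arms are recorded on the case report form whatever the suspected cause; relatedness is judged separately, blind to celecoxib/placebo allocation; and events are tabulated by randomised arm.

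Do not attach a week-2 end to recording. The Patient safety section sets no end date, and the Interventions section offers placebo and waiting-list patients celecoxib or acupuncture after the 2 weeks. A cutoff there would leave out events during that treatment.

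The form already includes adverse events, so the cost is the sentence itself and slightly more recording work. The change concerns data capture only and alters no treatment.
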